## Abstract

**Background:**

Adults with autism spectrum disorder (ASD) are at increased risk for chronic health conditions and reduced quality of life (QoL), often linked to lower physical activity (PA), motor impairments, and barriers to health care access. Although communication and social differences in ASD are well documented, motor impairments such as deficits in coordination, balance, and gait remain understudied in adulthood despite their relevance to fall risk and PA participation. Telehealth and wearable technologies may improve access to physical therapy assessment and remote monitoring of physical function in this underserved population.

**Objective:**

This pilot study aims to evaluate the feasibility, construct validity, and rating reliability of remotely administered physical function and balance assessments in adults with ASD and to examine racial and ethnic disparities and associations among physical function, PA, fall risk, and QoL.

**Methods:**

This pilot study uses a 2-phase, cross-sectional, noninterventional design with remote data collection in legally independent adults aged 18-59 years with ASD who were recruited through the Simons Powering Autism Research and Knowledge (SPARK) registry. Participants complete self-report questionnaires; 2 weeks of wearable step monitoring using a Fitbit Inspire 3 (Google LLC) device; and, for a randomized subset of 25 participants, 1 remote, telehealth-based physical function assessment session. Remote performance-based measures include the Five Times Sit-to-Stand, 30-second Sit-to-Stand, standing balance under eyes open and eyes closed conditions, and single-leg stance under eyes open and eyes closed conditions. Construct validity of the Patient-Reported Outcomes Measurement Information System (PROMIS) physical function measures will be examined using hypothesis testing with related indicators of health and functioning, including steps per day, lower-extremity functional outcome surveys, fall risk screening surveys, and comorbidity burden. Interrater and intrarater reliability of remote performance scoring will be evaluated from video-recorded sessions scored by 6 raters using intraclass correlation coefficients. Secondary analyses will examine racial and ethnic disparities in physical function, PA, and QoL, as well as associations among these variables and moderation by race and ethnicity.

**Results:**

Study funding was available from August 2024 to May 2025. Recruitment occurred from December 2024 to March 2025, and final data collection was completed in May 2025. By May 2025, 155 adults with ASD had been recruited, of whom 65.2% were female and 77% identified as Black or Hispanic. Data analysis is projected to be completed in July 2026, and submission of the primary results manuscript is anticipated in August 2026.

**Conclusions:**

This protocol describes a pilot study designed to evaluate the feasibility, construct validity, and equity relevance of remotely administered physical function assessments in adults with ASD. If supported, the findings may provide preliminary evidence for more accessible telehealth-based assessment approaches and inform larger studies on physical functioning, PA, and QoL in this population.

**International Registered Report Identifier (IRRID):**

DERR1-10.2196/86020

## Introduction

### Background

Autism spectrum disorder (ASD) is a lifelong neurodevelopmental condition characterized by persistent differences in social communication and interaction, alongside restricted and repetitive patterns of behavior and interests [1]. Beyond these core diagnostic features, many autistic individuals experience clinically meaningful motor impairments, including reduced coordination, poor balance, atypical gait, and diminished muscle strength [2-5]. These impairments often persist into adulthood and across the life course [6-9], yet they remain relatively underrecognized in adult ASD research and clinical care. Motor limitations may reduce participation in physical activity (PA), increase sedentary behavior, and contribute to an elevated risk of falls, obesity, and chronic health conditions, ultimately affecting overall functioning and quality of life (QoL).

Despite their relevance, motor impairments and physical function remain underresearched in adults with ASD. These domains are not included in diagnostic criteria, are inconsistently assessed in clinical practice, and are infrequently addressed through movement-based rehabilitation strategies [2,10,11]. The limited use of standardized, objective measures of physical function in autistic adults also restricts the ability to evaluate intervention effects, monitor change over time, and tailor supports to individual needs [10]. This gap underscores a pressing need for accessible, valid, and reliable methods to assess physical function and motor performance in adults with ASD.

Barriers to health care access further complicate the evaluation and management of physical function in this population. Adults with ASD often encounter communication challenges, sensory sensitivities, anxiety, and limited provider familiarity with adult ASD, all of which may interfere with effective assessment and treatment [12-14]. These barriers are often compounded for racial and ethnic minority populations, who may also experience delayed diagnosis, underrecognition of co-occurring conditions, and structural inequities in care [15-17]. Additional barriers related to transportation, geography, financial constraints, and health system complexity may further reduce participation in clinic-based care [18-20]. Telehealth-based approaches may help address these barriers by reducing logistical burdens, minimizing sensory and social stressors, and expanding participation in both research and clinical services.

Telehealth has emerged as a practical modality for functional assessment in both clinical and research settings. Synchronous telehealth allows for real-time administration and observation of performance-based measures, whereas asynchronous video review allows repeated observation, more detailed scoring, and evaluation of interrater and intrarater reliability [21-24].

Together, these approaches may improve accessibility while preserving observational rigor. However, although telehealth-based rehabilitation and remote monitoring are increasingly used, standardized evaluations of physical function in adults with ASD remain limited, and psychometrically supported remote assessment methods for this population are largely absent from the literature [2,10,11].

This protocol addresses this gap by examining the feasibility, construct validity, and rating reliability of remotely administered physical function assessments in adults with ASD. Consistent with the analytic plan, the study evaluates the construct validity of patient-reported physical function using related indicators of health and functioning, including PA, lower-extremity function, fall risk, and comorbidity burden, while also examining remote performance-based measures as exploratory complementary indicators of physical function. The protocol additionally investigates racial and ethnic disparities in physical function, PA, fall risk, and QoL and evaluates whether the relationships among physical function, PA, and QoL differ by race and ethnicity. By focusing on telehealth-delivered assessments and equitable inclusion of racial and ethnic minority participants, this study seeks to inform more accessible and inclusive approaches to physical function assessment in adults with ASD.

### Guiding Theoretical Model

This study is guided by the Model of Healthcare Disparities and Disability (MHDD**)** [25], which extends disability-focused frameworks by explicitly incorporating health care access, system-level barriers, and contextual influences on functioning and health outcomes.

Whereas the International Classification of Functioning, Disability, and Health (ICF) [26] recognizes the interaction among body functions, activity, participation, and contextual factors, the MHDD more directly emphasizes how mismatches between individual characteristics and environmental or health system conditions can contribute to reduced access to care, diminished functioning, and poorer health outcomes among people with disabilities (see Figure 1**)** [25]. Within this framework, remotely administered physical function assessment is conceptualized as a strategy to reduce environmental and health care access barriers that may disproportionately affect adults with ASD, particularly those from underserved or racial and ethnic minoritized groups. Telehealth may support participation by allowing assessment to occur in a familiar environment and by reducing transportation-related burden, clinic-related stress, and sensory overload. In this way, remote physical function assessment is positioned not only as a methodological innovation but also as a potential mechanism for improving access to health services relevant to physical functioning.

**Figure 1 figure1:**
[figure not shown]
This figure illustrates the theoretical framework informing the study, adapted from the original Model of Healthcare Disparities and Disability (MHDD). The red rectangle highlights the specific focus of this research: contextual barriers to health care access for individuals with disabilities. Remotely administered performance-based measures are designed to overcome these barriers to improve access and quality of health care, support optimal functioning, and enhance quality of life.

Although QoL is not represented as a discrete construct within the MHDD, it is closely related to the model’s emphasis on functioning, participation, and contextual fit of the individual. Inadequate access to appropriate health services, environmental barriers, and poor alignment between individual needs and care delivery may negatively influence functioning and participation, thereby affecting QoL. In this protocol, QoL is conceptualized as an important downstream outcome linked to physical function, PA, health burden, and access-related factors. The MHDD provides a useful framework for understanding how remotely delivered physical function assessments may support more equitable health evaluations and, ultimately, more responsive care for adults with ASD.

### Objectives

This paper presents the protocol for a pilot study designed to evaluate the feasibility, construct validity, and rating reliability of remotely administered physical function assessments in adults with ASD, with attention to racial and ethnic equity in participation and outcomes.

This study has three primary aims:

To evaluate the feasibility, construct validity, and rating reliability of remote physical function assessment in adults with ASD.
Construct validity will be examined primarily through hypothesis testing of the Patient-Reported Outcomes Measurement Information System–Physical Function (PROMIS-PF) measure against related indicators of health and functioning, including habitual PA, lower-extremity functional outcome surveys, fall risk screening surveys, and comorbidity burden. Remote performance-based measures will also be examined as exploratory complementary indicators of physical function. Interrater and intrarater reliability of remote performance scoring will be evaluated using video-recorded assessment sessions scored by multiple raters.To examine racial and ethnic disparities in physical function, PA, fall risk, and QoL among adults with ASD.
This objective is intended to generate preliminary evidence regarding differences in health and functioning across racial and ethnic groups within a telehealth-based study sample.To examine associations among physical function, PA, personal and environmental factors, and QoL, and to evaluate whether these relationships vary by race and ethnicity.
This objective will assess whether physical function and PA are associated with QoL and whether race/ethnicity moderates these relationships.

This protocol is intended to provide foundational evidence for more accessible, equitable, and scalable approaches to physical function assessment in adults with ASD. If the planned hypotheses are supported, the findings may inform future larger-scale studies and telehealth-based rehabilitation strategies aimed at improving physical function, PA, and QoL in this population.

## Methods

### Study Design and Procedures

This pilot study will use a 2-phase, cross-sectional, noninterventional design with remote data collection in adults with ASD, with targeted recruitment of individuals from underrepresented racial and ethnic groups. This study uses a nested design. The full sample of participants will complete the self-report and wearable activity monitoring components of the study. Within this overall sample, a randomized subset of 25 participants will also complete Phase 1, which consists of a remote telehealth-based performance assessment session. Accordingly, Phase 1 participants are included within the overall study cohort and are not treated as a separate sample.

### Ethical Considerations

This study was approved by the Institutional Review Board of Florida International University (Protocol #IRB-24-0230-AM5; TOPAZ Reference #113500). Electronic informed consent will be obtained from all participants prior to study participation. Participant data will be deidentified and handled in accordance with institutional and applicable regulatory requirements for privacy and confidentiality. Data were securely stored and managed using REDCap (Vanderbilt University).

### Study Population

Eligible participants will be adults with a self-reported professional diagnosis of ASD registered in the Simons Powering Autism Research and Knowledge (SPARK) registry. SPARK is a nationwide database of individuals residing in the United States and will serve as the recruitment source for this study [27]. The registry has demonstrated high diagnostic validity (98.8% agreement rate) [28] and includes over 13,000 adults, approximately 55% of whom are legally independent. Participants will be required to have access to a personal computing device with internet connectivity and the ability to complete remote assessments.

### Inclusion/Exclusion Criteria

The inclusion criteria are legally independent adults with ASD aged 18-59 years, with a previous professional diagnosis or educational classification of ASD, autism/autistic disorder, Asperger syndrome, or pervasive developmental disorder not otherwise specified. Participants will be registered with the SPARK network, and their available registry data must include age at registration, sex, race, ethnicity, professional or professionals who provided the ASD diagnosis, age at initial diagnosis, lifetime receipt of services, participation in an individualized education program or other ASD-specific programs, and autism severity as measured by the Social Responsiveness Scale (SRS). Persons will be excluded from the study if they have any open wounds, fractures, severe visual or hearing impairments, or health conditions that prevent them from standing up from a chair or standing on either leg or that preclude safe participation in remote assessment.

### Recruitment

To target the recruitment of adults with ASD from underrepresented racial and ethnic groups, we will implement a multipronged strategy in collaboration with the SPARK Research Match service. Research Match, an integrated service of the Simons Foundation Autism Research Initiative (SFARI), enables approved investigators to recontact SPARK participants for new studies. The platform supports both remote and in-person research and streamlines enrollment by integrating invitation, eligibility screening, and survey access into a single system. Recruitment will be conducted via email outreach through SPARK’s “batched recruitment” infrastructure, which allows invitations to be distributed in waves to selected subsets of eligible participants until the enrollment targets are met. Stratified sampling will be used to ensure the representation of Black/African American and Hispanic/Latino participants, with random selection continuing until quotas of 50 participants per group are achieved.

Eligible individuals will be invited to review and electronically sign informed consent forms. We plan to enroll a total of 155 participants. All enrolled participants will complete the self-report and wearable activity monitoring components of the study. Within this overall sample, a randomized subset of 25 participants will be invited to complete the Phase 1 remote telehealth-based performance assessment session. Thus, the Phase 1 subset is nested within the full study sample.

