### Self-Report Surveys

#### Demographic Characteristics

Demographic variables, including race and ethnicity, state, ZIP code, and sex, will be collected via surveys to support stratified and moderation analyses.

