### Statistical Data Analysis Plan

All analyses will be conducted using 2-sided tests with a significance level of α=.05. Descriptive statistics will summarize participant characteristics and study variables. Continuous variables will be summarized using means and standard deviations or medians and interquartile ranges, as appropriate, and categorical variables using frequencies and percentages. Prior to inferential analyses, assumptions of normality, linearity, homoscedasticity, and absence of multicollinearity will be evaluated. If the assumptions for parametric analyses are not met, appropriate nonparametric or robust analytic methods will be applied.

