An a priori power analysis was conducted using G*Power (version 3.1.9.7; Heinrich Heine University Düsseldorf) [63]. Assuming a 2-tailed α=.05 and power=0.80, a total sample size of N=155 provides adequate power to detect small-to-moderate correlations (r ≥ 0.25-0.30), consistent with expected construct validity effect sizes. PROMIS-PF scores are expected to demonstrate moderate positive correlations with habitual PA and performance-based functional measures and moderate-to-strong positive correlations with other self-reported function scales. Negative correlations are anticipated with fall risk indicators and comorbidity burden. In addition to the power-based justification, precision was considered. At N=155, correlation estimates are expected to have reasonably narrow 95% CIs, supporting adequate precision in estimating associations [64].

The sample size for reliability analyses was informed by Borg et al [59]. Assuming 2 repeated measurements per rater, a subsample of n=25 is expected to provide sufficient precision to estimate ICC values ≥0.75, consistent with recommendations for reliability studies.

The full sample (N=155) will be used for primary construct validity analyses, while the nested subset (n=25) will support exploratory performance-based validity analyses and reliability estimation.

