#### Aim 2: Racial and Ethnic Disparities in Physical Function, PA, and QoL

To examine racial and ethnic disparities in physical function, PA, personal and environmental factors, and QoL among adults with ASD, analysis of covariance models will be used to compare adjusted mean outcomes between non-Hispanic White participants and participants from racial and ethnic minoritized groups. Covariates such as sex and autism severity will be included as appropriate to reduce confounding. If analyses are expanded to include more than 2 racial and ethnic groups, omnibus models will first be conducted, followed by multiplicity-adjusted pairwise comparisons where the overall test is statistically significant. Effect sizes and 95% CIs will be reported alongside *P* values. The planned sample size of 155 participants is expected to provide adequate power to detect medium-sized effects and to generate preliminary disparity estimates for future studies [63].

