#### Aim 3: Associations of Physical Function, PA, Personal and Environmental Factors, and QoL, and Moderation by Race and Ethnicity

To examine the associations among physical function, PA, personal and environmental factors, and QoL, multiple linear regression analyses will be performed with QoL as the dependent variable. The primary independent variables will include PROMIS-PF and habitual PA (steps per day), with additional personal and environmental factors entered as indicated by the conceptual model. Covariates such as sex and autism severity will be included as appropriate. We hypothesize that better physical function and greater PA will be associated with better QoL. To evaluate moderation by race and ethnicity, interaction terms between race/ethnicity and physical function, as well as between race/ethnicity and PA, will be entered into the regression models. Continuous predictors will be centered prior to the creation of interaction terms to improve interpretability and reduce multicollinearity. When significant interactions are identified, simple slopes or stratified analyses will be used to further characterize the nature of the moderation effect. Model results will be reported using unstandardized and standardized regression coefficients, 95% CIs, *P* values, and model fit statistics (eg, adjusted *R*^2^). The same a priori power analysis described above applies to aim 3; although this pilot study may be underpowered to detect small effects, it is expected to provide preliminary effect size estimates to guide future research [63].

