## Results

### Overview

Funding for this study was active from August 2024 through May 2025. Participant recruitment was conducted from December 2024 to March 2025, and final data collection was completed in May 2025. As of May 2025, 155 participants had been recruited into the study. Figure 3 summarizes participant recruitment and enrollment. Data analysis is projected to be completed by July 2026, and the primary study results are anticipated to be submitted for publication in August 2026.

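### Steps/day comes from one 2-week winter-to-spring window per participant, and the Aim 2 comparison by race/ethnicity names no wear-date term

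*Protocol article*

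**What the plan says.** **Measurement.** Under Design of Functional Assessment and Self-Report Surveys Testing, every participant is mailed a monitor and wears it for 2 weeks. Free-Living Daily PA (Steps/Day) accepts 7 valid days (5 weekdays and 2 weekend days) with at least 10 waking hours.

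**Calendar and place.** Results, Overview: "Participant recruitment was conducted from December 2024 to March 2025, and final data collection was completed in May 2025". Study Population describes the registry as covering the whole United States.

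**Recruitment.** The batched system "allows invitations to be distributed in waves to selected subsets of eligible participants until the enrollment targets are met". The same section plans stratified sampling with quotas of 50 Black/African American and 50 Hispanic/Latino participants.

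**Analysis.** Aim 2 compares adjusted means between non-Hispanic White and minoritized participants, and states: "Covariates such as sex and autism severity will be included as appropriate to reduce confounding". Aim 3 uses the label again: "The primary independent variables will include PROMIS-PF and habitual PA (steps per day"; it also lets personal and environmental factors into the model. Aim 1 calls steps/day habitual as well.

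**Location data.** Demographic Characteristics: "Demographic variables, including race and ethnicity, state, ZIP code, and sex, will be collected via surveys to support stratified and moderation analyses".

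Season, wear date and recruitment wave appear neither in the Statistical Data Analysis Plan nor under Strengths and Limitations.

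**The concern.** Walking may vary with cold and daylight. A 2-week count in January need not measure the same thing as one in May, and no participant is measured in summer or autumn. A single such window is thin support for the label *habitual*.

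The consequence that matters is in Aim 2. If one racial or ethnic group tended to wear the device earlier in the year than another, part of any seasonal difference in steps would appear as a disparity in physical activity, or would hide a real one. Neither named covariate, sex or autism severity, addresses this. Enrolment in batches with stratified sampling makes such an imbalance possible, and nothing in the plan checks for it. Aim 2 is meant to supply preliminary disparity estimates for future studies, so a bias would be carried forward.

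In Aims 1 and 3, season unrelated to physical function adds noise to steps/day and weakens associations.

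**Working it through.** **1. The plan's own sample-size figure.** The article states that "a total sample size of N=155 provides adequate power to detect small-to-moderate correlations (r ≥ 0.25-0.30", with "Assuming a 2-tailed α=.05 and power=0.80". By Fisher's z, n = ((1.960 + 0.842)/atanh(r))² + 3:
- r = 0.25 needs 124, and power at N = 155 is 0.88;
- r = 0.30 needs 85, and power at N = 155 is 0.97.

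The statement holds, with margin.

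**2. Precision of the Aim 2 contrast.** Results, Recruitment gives 34 non-Hispanic White participants and 79 + 40 + 1 = 120 minoritized participants; one person did not report. In SD units and without covariates, SE = √(1/34 + 1/120) = √(0.0294 + 0.0083) = 0.194.

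**3. Size of a seasonal bias.** The article gives no wear dates by group and no seasonal step figures, so these inputs are assumptions:
- winter-to-spring difference S: 500 to 1,500 steps/day;
- SD of steps/day: 3,500;
- difference D between groups in the share worn in spring: 0.20 to 0.40.

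Bias = S × D.
- Low end: 500 × 0.20 = 100 steps/day; 100/3,500 = 0.03 SD.
- High end: 1,500 × 0.40 = 600 steps/day; 600/3,500 = 0.17 SD.
- D = 0: no bias, whatever the value of S.

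The high end is 0.171/0.194 = 0.88 standard errors. It is about one third of a medium effect, taking medium as 0.5 SD (the article gives no figure).

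**4. Effect on the test.** With no true difference, the two-sided 5% rejection rate is 1 − Φ(1.96 − bias/SE) + Φ(−1.96 − bias/SE).

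| Bias (SD) | Rejection rate |
|---|---|
| 0 | 0.050 |
| 0.03 | 0.052 |
| 0.10 | 0.081 |
| 0.17 | 0.143 |

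The 0.10 row corresponds, for example, to a seasonal difference of 0.2 SD with D = 0.5.

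**5. Effect on Aims 1 and 3.** Suppose season is unrelated to physical function and half the sample is measured late. A seasonal difference of g SD then multiplies a correlation by 1/√(1 + g²/4). For g = 0.2 to 0.5, a true r of 0.30 becomes 0.299 to 0.291. Power at N = 155 for r = 0.291 is still 0.96. The calculation is for a simple correlation; it indicates the order of the effect on Aim 3.

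**The case against.** The strongest reply is that nothing shows an imbalance. A reader might infer that waves were sent out by race/ethnicity. Recruitment does not say so: it describes a platform that permits waves, and separately a stratified sample with quotas for two groups and none for the non-Hispanic White reference group. Enrolment of 79 Black/African American and 40 Hispanic participants, against quotas of 50, shows nothing about when each group wore the device. This stands: the bias is a possibility, not a finding.

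A reader might also infer that place is ignored altogether. It is not. State and ZIP code are collected for stratified and moderation analyses, Table 1 classes them as personal/environmental factors, and Aim 3 admits such factors. Only the Aim 2 step comparison lacks a named place covariate. Routine regional adjustment there is debatable, because the Guiding Theoretical Model treats context as a contributor to disparities; conditioning on region could remove part of what Aim 2 sets out to describe. This too stands.

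Third, the Aim 2 covariate list is open-ended, and an article may leave its completion to a fuller plan. That is fair, and the point is therefore not that the list is short. It is that one specific, plausible confounder of steps/day is addressed by neither named covariate and can be handled with data already held.

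Finally, the article describes itself as preliminary and hypothesis-generating, requires both weekday and weekend wear, and makes no year-round claim. That lowers the stakes, but the label *habitual* and the absence of any limitation about the single window remain.

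**Conclusion.** The point holds as a modest, conditional one. Steps/day describes one 2-week window between winter and late spring; it is called habitual and compared by race/ethnicity with no wear-date term named. If wear dates are balanced across groups, the seasonal bias in Aim 2 is zero. Under the assumed inputs it is 0.03-0.17 SD, below one standard error of the 34 versus 120 comparison, and the false-positive rate rises from 0.05 to at most about 0.14. The Aim 1 and Aim 3 associations are little affected: an r of 0.30 stays at or above 0.29 for seasonal differences up to 0.5 SD.

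The seasonal difference, the SD and the imbalance are all assumptions; larger values would give a larger bias. The documents do not support saying that the Aim 2 comparison is confounded, only that the named covariates do not guard against it.

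**What to change.** 1. Tabulate wear month and region by race/ethnicity before fitting the Aim 2 steps/day model.
2. Add one low-df wear-date term to that model: the midpoint date of wear, or day length derived from date and ZIP code. A separate term for each calendar month from December to May would use up to 5 df and is not needed.
3. Report adjustment for region only as a sensitivity analysis, since place may be part of the disparity being described.
4. Describe the measure as steps/day over a 2-week winter-to-spring window, and list the single window under Strengths and Limitations.

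The cost is about 1 df and one extra table. Dates come with the daily step downloads, and state and ZIP code are in the survey, so no further data collection is needed. No change to the Aim 1 correlation analysis is required.
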